**Outcome measures**

Primary outcome measures include laboratory assessments of nicotine reinforcement and smoking cue reactivity. The measure of nicotine reinforcement is the percentage of nicotine cigarette puffs chosen during the forced-choice task. Measures of cue reactivity include tobacco craving, mood, and autonomic responsivity.

The secondary outcome measure is days of smoking abstinence during the quit-attempt weeks. Abstinence is assessed by self-reports of no smoking and by breath carbon monoxide < 5 ppm. Other assessments of abstinence include self-reported tobacco craving and withdrawal.

Sociodemographic and baseline measures (e.g., smoking history, level of nicotine dependence, number of cigarettes smoked per day, tobacco craving, mood, smoking motivations) will be used to characterize the sample and explore as mediators of primary and secondary outcomes.

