**Statistical Analysis**

Standard techniques will be used to examine the distributional properties of the data (means, standard deviations, medians, skewness, kertosis) in order to verify that all assumptions are met for subsequent analyses. The data will be examined for univariate and multivariate outliers. For all analyses, results are considered significant at *p*<.05.

Aim 1:Investigate the effect of gemfibrozil on laboratory measures of nicotine reinforcement and cue-elicited craving

The percentage of puffs chosen from Nic cigarettes in the forced-choice sessions will be analyzed using mixed-model analysis of variance (ANOVA) with drug condition (placebo, gemfibrozil) as within-subject factors and order of exposure of drug condition and order of exposure of cigarette type (Nic, Denic) as between-subject factors. For cue-reactivity sessions, self-report and physiological measures will be analyzed by mixed-model ANOVA, with drug condition (placebo, gemfibrozil), cue type (smoking, nonsmoking) and time post-cue (0, 15 minutes) as within-subject factors and order of exposure of drug condition and cue type as between-subject factors. For measures showing significant main effects or interactions, post hoc comparisons between means will be conducted. Supplemental analyses may be conducted using bivariate analyses to identify relationships to participant-level variables (e.g., socioeconomic factors, mood). Variables identified will be used as covariates if they are believed to be suppressor variables or entered into stepwise regressions to better characterize the participants for whom gemfibrozil has the greatest effect on laboratory measures.

Aim 2: Screen for the ability of gemfibrozil to aid smoking abstinence during a brief quit attempt

Data from the quit-attempt will be analyzed using mixed-model ANOVA with drug condition (placebo, gemfibrozil) as a within-subject factor and order of exposure of drug condition as a between-subject factor. Post hoc comparisons between means will be conducted on significant overall effects. Supplemental analyses may be conducted using bivariate analyses to identify relationships to participant-level variables (e.g., socioeconomic factors, mood). Variables identified will be used as covariates if they are believed to be suppressor variables or entered into stepwise regressions to better characterize the participants for whom gemfibrozil facilitates smoking abstinence.

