Aim 3: Examine the validity of using laboratory measures of tobacco dependence to predict smoking abstinence and possible gemfibrozil-related increases in smoking abstinence

Bivariate correlational analyses will be used to determine the predictive association between laboratory measures of nicotine reinforcement and cue reactivity and tobacco abstinence during the quit-attempt. Two multivariate stepwise regressions will then be constructed to determine multivariate predictors of abstinence days and gemfibrozil-related change in abstinence days. At step one, demographic variables will be entered. At step two, smoking-related characteristics that are significantly associated with abstinence will be entered. Finally, at step three, measures of laboratory performance in both forced-choice and cue-reactivity that were significant in bivariate analyses will be entered to determine their multivariate predictive validity for smoking abstinence.

Power Analysis

Based on the preclinical data, we expect that gemfibrozil will decrease cue-reactivity, the number of puffs taken on the nic cigarette and increase abstinence. The preclinical data suggest that observed effect size of those effects will be around 0.5. However, those effect sizes may be lower in human subjects. As we have currently no data on human subjects, we decided to power the study to be able to detect a smaller effect size. Taken into account the variance of the behavioral responses based on the previous human laboratory studies (McKee et al., 2011), with 40 subjects, we will have sufficient power (>80%) at an alpha level of 0.05 to detect differences between conditions (gemfibrozil vs placebo) as small. This study will provide the necessary data to determine the effect size of gemfibrozil on these measures and preliminary evidence on the potential utility of gemfibrozil as a smoking cessation pharmacotherapy. Based on the results obtained, we can submit further grants to conduct a clinical trial to investigate the efficacy of gemfibrozil as a smoking cessation medication.

Missing, unused and spurious data:

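### Aim 3 picks laboratory predictors by their p-values and then tests them in the same sample, and its change-score regression leaves out treatment order

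*Protocol*

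**What the plan says.** The Aim 3 paragraph starts with bivariate correlations between the laboratory measures and abstinence. It continues: "Two multivariate stepwise regressions will then be constructed to determine multivariate predictors of abstinence days and gemfibrozil-related change in abstinence days".

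Three steps are listed:

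- First step: "At step one, demographic variables will be entered".
- Second step: "smoking-related characteristics that are significantly associated with abstinence will be entered".
- Third step: "measures of laboratory performance in both forced-choice and cue-reactivity that were significant in bivariate analyses will be entered to determine their multivariate predictive validity".

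The threshold comes from the opening of the section: "For all analyses, results are considered significant at" p < .05. The Aim 3 text mentions no hold-out sample, cross-validation or multiplicity adjustment.

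Treatment order is a between-subject factor in the Aim 1 and Aim 2 ANOVAs. It is not in the Aim 3 steps. Under Considerations of a Crossover Design the protocol says that data will be analysed for order as a test of carryover, without linking this to Aim 3.

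Hypothesis 4 expects the laboratory measures to be negatively associated with days abstinent. Hypothesis 5 extends this to the gemfibrozil-placebo differences.

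**The concern.** The protocol states a procedure here; it does not leave a gap for a later plan. A measure reaches step three only because it was already significant in these participants, and the step-three result is then read as evidence of its predictive validity. A test computed after selection on nearly the same test does not keep its nominal 5% error, and the explained variance is inflated in the same way.

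The change-score regression has a second, separate problem. A gemfibrozil-minus-placebo difference contains the period effect with one sign in participants who take gemfibrozil first and with the other sign in those who take placebo first. If both the laboratory measure and abstinence drift between phases, their differences move together across the two orders even when no association exists within either order. An order term removes this, and the listed steps have none.

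What is at stake is the claim that laboratory measures predict quitting. The introduction concedes that earlier work found little predictive association between cue-elicited craving and relapse, so a false positive would be easy to mistake for the novel finding.

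**Working it through.** **The plan's own figure.** There is none for Aim 3. The Power Analysis gives more than 80% power with 40 subjects for the gemfibrozil-placebo difference, without a numerical effect size. A paired t-test at n = 40 reaches 80% at a standardised difference of 0.454. That figure does not bear on Aim 3.

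**Inputs from the protocol.**
- Threshold p < .05 (taken as two-sided).
- Enrolment up to 40; 30 completers in the enrolment table; attrition up to 50%, with drop-outs replaced. The calculations use n = 30.
- Cue-reactivity measures: TCQ-SF, Mood Form, four VAS items and four physiological signals, which makes 10. The forced-choice percentage brings this to 11. Counting the 10 cue measures at both post-cue times gives 10 × 2 + 1 = 21.

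**Assumptions.** The protocol does not fix the number of candidate measures. I take 13, within the range of 11 to 21, with correlations of 0.3 to 0.5 and four demographic covariates at step one, all unrelated to the outcome.

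**Part 1: screen and refit**

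1. The bivariate screen at n = 30 passes |r| > t/√(t² + 28) with t = 2.048, that is 2.048/√32.19 = 0.361.
2. If the measures were independent, the chance of at least one false pass per outcome would be 1 − 0.95^K: 43.1% for K = 11, 48.7% for K = 13, 65.9% for K = 21.
3. With 13 measures correlated 0.3 to 0.5, simulation gives 35-40%.
4. Entering the survivors at step three after the four demographics, the step-three F test is significant in 19-25% of null trials, against 5% nominal. All selected measures have the hypothesised negative sign in 10-12%. Repeat simulations under the same assumptions gave 18-28% and 9-13%.
5. A wider grid (n = 20, 30, 40; 5, 11 or 21 measures; correlation 0 or 0.5) puts a false step-three coefficient in 9-49% of null trials. When something has been selected, the mean spurious partial R-squared is 0.15-0.37, and about 0.22 for 11 measures at n = 30.

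**Part 2: treatment order**

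Let s = +1 or −1 by order, with equal allocation. Write the laboratory difference as δ_L·s plus noise and the abstinence difference as δ_A·s plus noise. The noise terms are independent with SD 1, so each shift is in SD units of the within-person difference. Then

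spurious r = δ_L·δ_A / √[(1 + δ_L²)(1 + δ_A²)].

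| Shift in both | Spurious r | False positives, n = 30, no order term | With order term |
| --- | --- | --- | --- |
| 0.2 SD | 0.04/1.04 = 0.038 | 5.6% | about 5% |
| 0.3 SD | 0.09/1.09 = 0.083 | 6.8% | about 5% |
| 0.5 SD | 0.25/1.25 = 0.20 | 18.8% | about 5% |

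If only one of the two measures shifts, δ_L·δ_A = 0 and the rate stays at 5.0%. At 0.5 SD in both, the rate without order is 13.4% at n = 20 and 24.0% at n = 40, so a larger sample does not help.

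The sign of the artefact is the sign of δ_L·δ_A. Shifts in the same direction give a positive correlation: at 0.5 SD and n = 30, 18.6% of trials are significantly positive and under 0.1% significantly negative. Shifts in opposite directions give the mirror image.

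**The case against.** Several objections carry weight.

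- **False predictors are not certain.** A reader might infer that spurious predictors will appear. Under the main assumptions above, most null trials produce no significant step three. If the whole model is tested instead of step three, the demographics dilute the effect and the rate is 8-11%. The supportable statement is a materially raised risk.
- **Direction.** A reader might infer that the missing order term favours Hypothesis 5. Hypothesis 5 follows on from a predicted negative association, and same-direction period shifts produce a positive one. The artefact would support the hypothesis only if the two period effects ran in opposite directions, and the protocol gives neither sign nor size. About half of the chance hits under Hypothesis 4 also have the wrong sign.
- **Order is mentioned, and a SAP may add it.** The crossover section does promise an analysis by order, but as a carryover test. The Aim 3 steps are written out without order, while Aims 1 and 2 name it in their models.
- **Sample size.** A final n of 20 needs 50% attrition without replacement, and the protocol plans replacement. Hence n = 30 here.
- **Standing of Aim 3.** It concerns neither the primary nor the secondary outcome, and the protocol describes its results as preliminary. This limits the consequence. Aim 3 is still one of three stated aims, with two hypotheses.

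Two wider readings do not hold. The optional supplemental analyses, "entered into stepwise regressions to better characterize the participants for whom gemfibrozil has the greatest effect on laboratory measures", might be taken to find prognostic variables and not modifiers of the drug effect. The text names no dependent variable, and a drug-placebo difference is equally compatible with it. Baseline measures that "will be used to characterize the sample and explore as mediators of primary and secondary outcomes" might look like a causal error, but the phrase refers to outcomes and not to a treatment effect, so it is a matter of terminology.

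**Conclusion.** The concern holds in limited form. The Aim 3 rule of selecting laboratory measures by p-value and judging them in the same sample raises the step-three false-positive rate to about 19-25% against 5% nominal, with about half of those results in the hypothesised direction, and inflates R-squared. This rests on 13 null measures correlated 0.3 to 0.5, four demographics and n = 30. The counts and correlations are assumptions, and the rate moves with them.

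The change-score regression as listed is also open to confounding by period. The inflation is slight for shifts of 0.2 or 0.3 SD and substantial at 0.5 SD (about 19%). It arises only if both the laboratory measure and abstinence shift, and it can take either sign. The documents give no period-effect size, so this is an avoidable exposure and not a demonstrated bias. Both points deserve correction because the steps are stated explicitly and the correction is cheap.

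**What to change.** In the Aim 3 paragraph:

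1. Add treatment order at step one of the regression for gemfibrozil-related change in abstinence days.
2. Name a small set of laboratory predictors in advance, for example the percentage of nicotine puffs and one cue-craving score. Keep them in the model whatever their bivariate p-values, and report estimates with confidence intervals.
3. Report all other laboratory measures as exploratory, with cross-validated R-squared or a multiplicity adjustment. A Bonferroni adjustment over 11 measures would use 0.05/11 = 0.00455 per test and raise the |r| needed at n = 30 from 0.36 to 0.50.

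The cost is a change of wording and slightly different regressions on the same data, with no added participants or visits. The downside is that fewer predictors can be claimed. Mood and autonomic measures, which the protocol lists among the primary outcomes, would be exploratory as predictors in Aim 3 unless they are among those named; their Aim 1 analyses are unaffected.

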The crossover design creates a special case in which a participant may successfully maintain abstinence during the first quit attempt. Although participants always have the autonomy to discontinue study participation, this is one situation where it could benefit them to do so. Thus, participants who successfully maintain abstinence during the first phase will meet with the PI or their designee to discuss discontinuing their participation. Participants will be informed of the dangers of returning to smoking and the benefits of continued abstinence. Participants will be informed of the treatment opportunities that are available to them, but that they cannot continue on study medication. Referrals for further treatment, both pharmacological and behavioral, will be provided. Participants will be encouraged to drop out of the study and continue smoking abstinence, but will not be arbitrarily discharged from the study. This procedure strikes a balance between two fundamental ethical principles of clinical research, beneficence and respect for the autonomy of the participant.

Withdrawal of subjects:

Stop points for withdrawing participants from the study include: 1) at the request of the participant, 2) if the participant is unable or unwilling to comply with study requirements and procedures, 3) any occurrence that in the opinion of the investigators would compromise the health of the participant, 4) any serious adverse effect; and 5) a successful quit attempt after the first phase of the study, meaning that the participant does not complete the second phase of the study.

When a subject is withdrawn from a study, data collection will cease with the exception of monitoring for adverse events and follow-up to check up on health, especially in the event where the participants withdrew for health reasons. Subjects will be replaced in the sense that attempts will be made to meet the target enrollment and continue to recruit until this has been met.

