Missing data will be dealt with according to statistical principles for filling in missing cells. In the event that large amounts of data are missing due to, for example, participant noncompliance with study procedures, the data will be analysed according to the primary goals of the study and the objectives of this study. Statistical procedures that deviate from the protocol will be reported and justified in a protocol deviation log.

The data from all eligible subjects will be included in the data analysis

Accrual Number

There are several factors that could adversely affect accrual and completion of this study: a) participants may quit during the first medication phase; b) some participants might experience intolerable side effects of gemfibrozil; and c) some participants might not be compliant with taking medication. Given these factors, we anticipate up to 50% attrition. Drop-outs will be replaced.

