**Human Subjects Protections**

Equity of Subject Selection

Participants will be enrolled without regard to sex, race, or ethnicity. Efforts will be made to include ethnic minorities in proportion to their presence in the metropolitan Toronto area (http://www.toronto.ca/demographics/index.htm). Targeted enrollment figures for Toronto are shown below.

Targeted enrollment figures for Toronto are shown below.

| **APPROVED STUDY POPULATION** | | | | | | |
| --- | --- | --- | --- | --- | --- | --- |
|  | FEMALE  ENROLLMENT | MALE  ENROLLMENT | **TOTAL**  ENROLLMENT | FEMALE  COMPLETERS | MALE  COMPLETERS | **TOTAL**  COMPLETERS |
| **APPROVED**  **CEILING** | 20 | 20 | 40 | 15 | 15 | 30 |

| **TARGETED/PLANNED ENROLLMENT** | | | |
| --- | --- | --- | --- |
| **ETHNIC CATEGORY** | Sex/Gender | | |
|  | Females | Males | Total |
| Hispanic or Latino | 1 | 1 | 2 |
| Not Hispanic or Latino | 19 | 19 | 38 |
| **Ethnic Category: Total of All Subjects*** | 20 | 20 | 40 |
| **RACIAL CATEGORIES** |  |  |  |
| American Indian/Alaska Native | 0 | 0 | 0 |
| Asian | 1 | 1 | 2 |
| South Asian | 1 | 1 | 2 |
| Black or African American | 1 | 1 | 2 |
| White | 17 | 17 | 34 |
| **Racial Categories: Total of All Subjects*** | 20 | 20 | 40 |

Exclusion Justifications

Smokers indicating no plans to quit smoking in the next 3 months, receiving smoking cessation treatment, or using any medications to help them quit smoking will be excluded because the study requires participants to make a quit attempt. Heavy drug and alcohol use could potentially confound responses to smoking cues and reinforcing effects of cigarettes. Children will be excluded because smoking under age 19 is illegal, and it is unethical to encourage teenage smoking. Pregnancy and nursing are exclusionary because smoking is toxic to fetal and infant development and the effect of gemfibrozil on pregnancy and nursing mothers is unknown.

Qualifications of Investigators and Study Staff

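### The >80% power claim counts 40 complete within-person pairs, which does not fit the protocol's own ceiling of 40 enrolled and 30 completers or its expected attrition of up to 50%

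*Protocol*

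**What the plan says.** Under Statistical Analysis, Power Analysis, the protocol first gives the preclinical expectation: "The preclinical data suggest that observed effect size of those effects will be around 0.5". Because effects in humans may be lower, the authors continue: "we decided to power the study to be able to detect a smaller effect size". The claim follows: "with 40 subjects, we will have sufficient power (>80%) at an alpha level of 0.05 to detect differences between conditions". No effect size, SD, within-person correlation or sidedness stands beside it. The variance is attributed to a cited human laboratory study.

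Four other places bear on the number 40:

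- **Participants:** enrolment is up to 40.
- **Human Subjects Protections, approved study population table:** the ceiling row (female, male and total enrolment, then female, male and total completers) reads "20 | 20 | 40 | 15 | 15 | 30".
- **Statistical Analysis, Accrual Number:** "Given these factors, we anticipate up to 50% attrition. Drop-outs will be replaced".
- **Participant Safety Monitoring, Withdrawal of subjects:** replacement is explained as "attempts will be made to meet the target enrollment and continue to recruit until this has been met".

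Study Design and Methods describes a two-period crossover with half the participants in each order. Statistical Analysis makes drug condition a within-subject factor. The primary outcomes are the laboratory measures, taken after the first medication week of each phase.

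**The concern.** A within-person contrast between gemfibrozil and placebo is informed by people who supply the measurement in both phases. Someone seen in only one phase gives no difference. The number that matters for power is therefore the number with both laboratory sessions. The power statement uses 40, which is also the maximum that may be enrolled.

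Some of the loss is foreseen by the design. Accrual Number lists quitting in the first phase as a cause of attrition, and Participant Safety Monitoring says that people who quit successfully in the first phase will be encouraged to leave the study and stay abstinent.

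The stake is how the result is judged. The Power Analysis says the findings will inform whether to seek funding for a clinical trial. A reader who takes the power statement at face value would credit the study with more sensitivity to effects below 0.5 than its planned completer numbers give, unless inputs that the protocol does not state are favourable.

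**Working it through.** **Inputs from the protocol.** Alpha is 0.05, power is above 80%, and the number of subjects is 40. The preclinical effect is about 0.5 and the target is smaller than that. The ceiling is 40 enrolled and 30 completers, an implied loss of 1 − 30/40 = 25%. Attrition is up to 50%, so with no replacement 40 × (1 − 0.50) = 20 complete.

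**Assumptions, because the protocol is silent.** The test is two-sided. The effect is dz, the mean difference divided by the SD of the within-person differences. The test is a paired t with n − 1 degrees of freedom. Using n − 2 or n − 4 for the order factors moves the detectable effect by at most 0.007.

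**Formula.** Power = P(|T| > t(0.975, n − 1)), where T is noncentral t with n − 1 degrees of freedom and noncentrality dz × √n. At dz = 0.5:

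- n = 40: noncentrality 0.5 × √40 = 3.16, critical value 2.02
- n = 30: noncentrality 0.5 × √30 = 2.74, critical value 2.05
- n = 20: noncentrality 0.5 × √20 = 2.24, critical value 2.09

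**The plan's own figure first.** It cannot be strictly reproduced without an effect size and SD. It is attainable with 40 complete pairs: power is 87% at 0.5, and 80% is reached at 0.454, which is below 0.5.

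**The same calculation at the protocol's other numbers.**

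| Complete pairs | Smallest dz with 80% power | Power at 0.5 | Power at 0.4 | Power at 0.3 |
|---|---|---|---|---|
| 40 | 0.454 | 87% | 69% | 46% |
| 30 (approved ceiling) | 0.529 | 75% | 56% | 36% |
| 20 (50% attrition, no replacement) | 0.660 | 56% | 40% | 25% |

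An effect of 0.5 needs 34 complete pairs, and 0.4 needs 52.

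**What replacement would require.** Enrolled = completers ÷ (1 − attrition). For 40 complete pairs this is 40 ÷ 0.75 = 53.3, so 54 enrolled, at 25% attrition, and 40 ÷ 0.50 = 80 enrolled at 50%. Both exceed 40.

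**Sensitivity to the unstated inputs.**

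- *One-sided test, same scale.* Power at 0.5 is 93%, 85% and 70% for 40, 30 and 20 pairs. The smallest detectable dz is 0.40, 0.465 and 0.58.
- *Effect in between-person SD units, correlation ρ between phases (assumed), two-sided.* The detectable effect is the dz value times √(2(1 − ρ)):

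| ρ | 40 pairs | 30 pairs | 20 pairs |
|---|---|---|---|
| 0.3 | 0.54 | 0.63 | 0.78 |
| 0.5 | 0.45 | 0.53 | 0.66 |
| 0.7 | 0.35 | 0.41 | 0.51 |
| 0.8 | 0.29 | 0.34 | 0.42 |

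The detectable effect falls to 0.5 at ρ = 1 − (0.5/dz)²/2. For 30 pairs this is 1 − (0.5/0.529)²/2 = 0.55, and for 20 pairs 1 − (0.5/0.660)²/2 = 0.71. To go below 0.5, the correlation must be higher than that.

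**The case against.** A reader might infer that the study is underpowered even for 0.5, or that the promised power is not delivered. The protocol does not support so flat a statement. It does not say how 0.5 is standardised, which correlation applies or whether the test is one-sided, and it takes the variance from a study outside the document. With 30 pairs the claim survives under a one-sided test. It also survives if 0.5 is in between-person SD units and the correlation is above about 0.55, comfortably so at 0.7. With 40 complete pairs the sentence is true on the plain paired scale. This part of the objection stands: the power sentence contains no demonstrable arithmetic error.

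The protocol also states that drop-outs are replaced, so 20 pairs is not what it plans. That stands too, and the 20-pair row is a worst case without replacement. But replacement up to 40 pairs breaks the ceiling of 40 enrolled and 30 completers, so it does not settle the matter in favour of 40.

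Completers are not exactly the primary-analysis number. Someone lost during the final quit week has already supplied both laboratory sessions, so the number of usable pairs may lie somewhat above the number of completers. People who leave after the first phase are still lost to the comparison.

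A reader might also make much of the sentence that ends "at an alpha level of 0.05 to detect differences between conditions (gemfibrozil vs placebo) as small" with no value. A number may have been lost when the text was read from PDF, so nothing here rests on that gap.

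Finally, the protocol presents the study as preliminary evidence, and nothing in it says that a null result will be taken as proof of no effect. That limits the harm but does not make the figures agree.

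**Conclusion.** The point holds as an unreconciled conflict. The power statement treats all 40 subjects as complete pairs, while the protocol's own figures allow 30 completers under the ceiling, or 20 at the stated worst attrition without replacement. The enrolment ceiling leaves no room to replace up to 40 pairs.

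On the two-sided, within-person-difference scale, the smallest effect with 80% power rises from 0.45 at 40 pairs to 0.53 at 30 and 0.66 at 20. At the planned 30, the aim of going below 0.5 is not met on that scale, and power at 0.5 is 75%. The aim can be met at 30 only under more favourable inputs: a one-sided test, or an effect in between-person SD units with a correlation above about 0.55. At 20 pairs a one-sided test is not enough on the paired scale, and a two-sided test needs a correlation above about 0.71. The protocol states none of these inputs, so the >80% figure is unsupported at the planned completer number. It is not shown to be false.

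**What to change.** 1. Restate the power for the number expected to supply both laboratory sessions: 30 under the approved ceiling, with 20 as the worst case.
2. Give the effect size, its scale, the SD or within-person correlation, and the sidedness. On the two-sided, within-person-difference scale the text would give 0.53 with 75% power at 0.5 for 30 pairs, and 0.66 with 56% for 20, with those assumptions stated beside the figures.
3. Drop or qualify the claim of more than 80% power for effects below 0.5, unless the stated inputs support it at 30 pairs.
4. Say whether 40 means enrolled or completing, and whether replacements count against the ceiling.
5. Bring Participants, Withdrawal of subjects, Power Analysis, Accrual Number and the approved study population table into agreement.

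This is a change of wording. It needs no extra participants and no change to procedures. The only downside is a less favourable stated power.
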